### Randomisation

Participants will be randomly assigned to the R2C group or the control group with a 1:1 allocation ratio. Randomisation will be stratified by gender and will use a standard computer-generated “permuted blocks of variable size” scheme for each stratum. Randomisation lists for each stratum will be generated at the start of the study by the study statistician and linked to a unique identification code. The statistician who prepares the lists will play no other role in the delivery of the interventions. Allocations will be concealed in individual envelopes labelled with the unique identification code and opened (in consecutive order) by the designated researcher (Researcher 1) after the baseline assessment. Envelopes were used because at the time of trial design and start-up it was not feasible to implement a centrally managed, online randomisation system. The contents of an envelope cannot be discerned without opening the envelope, and monitoring of randomisation dates and within-stratum sequence numbers is conducted to ensure randomisation errors do not occur. Randomised participants will be assigned their unique identification code, which will be in a re-identifiable format. Participants’ identifying information collected during this study will be stored separately from trial data, while the unique identifying code will be attached to both. Participant information and trial data will be stored in separate locked filing cabinets located on the study premises.

Following randomisation, participants will be contacted by Researcher 1 and provided with an overview of their assigned protocol (i.e. R2C or control). Participants will not be told any details about the other intervention. Appropriate resources will be sent to the participant (*R2C intervention*: R2C self-help booklets [44, 45] + pamphlets [34, 46]; *control*: pamphlets [34, 46]). Hard copy materials will be posted to the participant (soft copy materials will be sent via email at the participants’ preference). An outbound telephone call will be scheduled within 7 days to commence the four to six R2C sessions with the participant’s dedicated R2C Counsellor (*intervention*), or to commence the four phone check-ins with Researcher 1 (*control*). The treatment period starts within 7 days of randomisation.

### Intervention

Participants randomised to the R2C intervention will receive telephone counselling (incorporating evidence-based interventions [47–50]), self-help resources and pamphlets (Fig. 4).

**Fig. 4 Fig4:**
[figure not shown]
R2C intervention [27, 42, 44, 45, 47–50]

Participants randomised to the control conditions will receive pamphlets and telephone contacts (Fig. 5).

**Fig. 5 Fig5:**
[figure not shown]
Control condition

In both the treatment and control conditions, the call duration will be recorded. Short Message Service (SMS) messages will be sent to remind participants of all pre-arranged telephone sessions, and five attempts at contact within 1 week will be made per scheduled phone session. R2C intervention calls will be made from Turning Point’s telephone and online services department, which is equipped with the infrastructure needed for outbound calls and call recording.

### Follow-up

Follow-up assessments will be conducted by Researcher 2. The first follow-up assessment will be performed at 4–6 weeks post-baseline. Follow-up assessments will also be performed at 3, 6 and 12 months. The assessment at 4–6 weeks post-baseline will take approximately 10 min to complete (Timeline Follow-back [TLFB], adverse events and additional treatment enquiry only). The next three follow-up assessments will take approximately 30 min to complete. For each follow-up, five attempts to contact the participant will be made within 2 weeks. Approximately 20% of the intervention group, selected using random start systematic sampling, will be asked to complete additional qualitative feedback post the 3 months follow-up.

### Loss to follow-up

Participants who cannot be contacted after five phone calls will be deemed to be missing at that data collection time point. Researcher 2 will attempt to contact participants again at the next data collection time point, following the same procedure, unless the participant actively withdraws.

### Retention

The study will use retention enhancement techniques suggested by previous studies [51, 52] to encourage retention in the intervention calls and follow-up assessments. Retention enhancement techniques will include active verbal commitment, flexibility in scheduled call times, weighting reimbursements according to the importance of collecting data at each time point and text message reminders before scheduled calls.

### Reimbursement

Participants will be reimbursed with vouchers as follows: AUD$20 for baseline assessment, AUD$20 for 4–6 weeks assessment, AUD$40 for 3 months assessment (primary outcome time point), AUD$20 for 6 months assessment, AUD$40 for 12 months assessment (last assessment) and AUD$10 for treatment evaluation/qualitative feedback (for those who are selected).

### Data collection

An electronic Case Report Form (eCRF) will be completed for each participant using REDCap (Research Electronic Data Capture [53]), summarising all screening and study data. REDCap is a secure, web-based application designed to support data capture for research studies (including case report forms, real-time data entry validation and audit trails).

### Trial monitoring

#### Treatment integrity

Training and supervision to ensure treatment fidelity will include a week-long training session focusing on competence and adherence to the R2C intervention and research procedures, as well as regular clinical supervision. All sessions will be digitally recorded, and an independent research assistant will rate fidelity of intervention sessions for 20% of participants using random start systematic sampling. During each intervention session, R2C Counsellors will complete a checklist of modules, exercises and homework activities completed, to assist with adherence with the intervention.

Training will be provided to Researcher 1 (who completes the control group telephone check-ins), and a script will be used to ensure that only past-week use of pamphlets is queried (i.e. no inadvertent individualised counselling). Supervision of Researcher 1 will occur to prevent “drift”, and call duration records will be checked intermittently.

#### Adverse events

All adverse events will be recorded between the time of consent and the final follow-up visit. Participants will be asked about adverse events at baseline, during each R2C session/control check-in and at each point of follow-up contact. Participants will also be encouraged to contact the research team if they are concerned about an adverse event.

#### Participant assessed as at risk of suicide

When a participant is assessed as being at high risk of suicidal behaviour (a Suicidal Ideation Attributes Scale [SIDAS] score of 21+), referral to appropriate support is immediate. Researchers are trained in the National Centre for Suicide Prevention Training two-day Applied Suicide Intervention Skills Training (ASIST) course to ensure they are equipped with the skills to respond to suicide risk. Researchers are trained to transfer the participant to an on-duty Turning Point helpline counsellor when immediate risk is identified in order for risk to be managed and responded to in accordance with the clinical service’s clinical protocol. R2C Counsellors are well trained and experienced in the management of suicide risk, and clinical governance of risk for the trial is managed in accordance with organisational risk management procedures.

#### Participant withdrawal/discontinuation

The right to withdraw without consequence is outlined during the consent process and in the PICF. Verbal revocation of consent can be provided by the participant, or a Revocation of Consent form can be completed, with the option to remove all of the participant’s previously collected data or just to remove consent for further data collection. No further contact with the participant will be initiated by the research team upon verbal or written revocation of consent.

In instances where it has been identified that a participant meets exclusion criteria during the study (e.g. active suicidality), and/or that it is not in the best interests of the participant to remain in the study, the Principal Investigator (a psychiatrist) will decide whether to withdraw the participant from the trial. If a participant is withdrawn by the Principal Investigator, the reasoning for this will be explained to the participant. The participant will be referred to the appropriate clinical services for treatment and support. No further data collection will occur, with the exception of the details regarding adverse events.

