	Psychological distress *K10*	Assessed by the Kessler Psychological Distress Scale (K10) [36]
	Quality of life *EUROHIS-QOL 8-item index* *AQoL-6D*	Assessed by the EUROHIS-QOL 8-item index [37, 57] and Assessment of Quality of Life (AQoL-6D) [38]
	Cost effectiveness *AQoL-6D* *WHO HPQ* *Health-care* *Resource Use* *Questionnaire*	The incremental cost of treatment will be compared to the incremental benefits of treatment in terms of the primary outcomes and the difference in quality-adjusted life years (QALYs; assessed by the AQoL-6D). Work performance and productivity will be assessed by items from the WHO Health and Work Performance Questionnaire short form (WHO HPQ) [40]. Healthcare resource use is assessed using items from the 3Mg trial’s Health-care Resource Use Questionnaire [41]
	Adverse events *Structured questions*	During baseline, scheduled intervention/control calls, and follow-up calls, participants will be asked general questions: *“Have you had any health concerns recently* (baseline)/*since the last time you had telephone contact for this study?”*, *“Have you felt unwell or different since the last time you had telephone contact for this study?”* and *“Do you have any specific worries or complaints about your health in general?”*, as well as more specific questions: *“Has your alcohol use changed?”* and *“Has your mood changed?”*
Additional measures/participant feedback	Barriers to help-seeking *Structured questions*	Perceived barriers to treatment-seeking for alcohol problems will be identified through an open-ended question (*“What are the reasons that you have not sought treatment for your alcohol use in the past?”*) and from a list of 15 barriers (e.g. financial, stigma, readiness for change) developed by Schuler et al. [58]
	Treatment participation and satisfaction *CEST TCU ENG*	Assessed by the Client Evaluation of Self and Treatment (CEST) short form (TCU ENG) [39] (approximately 20% of the R2C intervention group)
	Qualitative feedback *Structured questions*	Questions asked will include: *“Which parts, if any, of the telephone intervention sessions were most helpful to you? How were these most helpful?”* and *“What did you think about the delivery, format and duration of the telephone intervention sessions?”* (approximately 20% of the R2C intervention group)

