#### Statistical analysis plan

Data will be collated, cleaned and validated, using programmed edit checks, in a database that will be locked prior to the unblinding of the study statistician. The primary analysis will take place after all subjects, not known to have withdrawn or not deemed lost to follow-up, have had their 12 months assessments, based on the intention-to-treat principle (i.e. subjects’ data are analysed as randomised and as stratified). A “per-protocol” sensitivity analysis will be restricted to those subjects with at least one post-baseline assessment and, for subjects randomised to the R2C arm, participation in at least one structured telephone counselling session.

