The repeated measurements of the outcome variables will be analysed by fitting linear mixed models, with fixed effects for treatment and time, and their interaction, and random effects for subjects and assessments within subjects, using restricted maximum likelihood (REML). As well as accommodating missing values under the missing at random assumption, this method will allow the most suitable variance-covariance model for the repeated measures to be selected, using Akaike’s information criterion [63], and commonality of nonlinear trends over time to be explored via splines. The *F* test will be used to test for an overall group-by-time interaction, and the primary comparison, between groups, of their changes from baseline to 3 months follow-up will be based on a *t* test of the corresponding interaction contrast — this *t* test will utilise the predicted means and their variance-covariance matrix that are recovered from the fitted mixed model. Diagnostic plots of residuals will be assessed and, if deemed necessary, variance-stabilising transformations, such as the empirical logistic transformation, will be applied to the outcome variables and inferences will be based on the analyses conducted on the transformed scale. In a series of exploratory analyses, mixed models with covariates for gender, illicit drug use, extent of exposure to the intervention, exposure to other treatments or programs, level of psychological distress and, as appropriate, level of alcohol use at baseline will be fitted, including their interactions with treatment group, in order to identify moderating factors. A sensitivity analysis, to assess the impact of missing 3-month data on the primary outcome, will use a “tipping point” approach [63]. Categorical, ordinal and binary outcomes will be analysed in a similar way using generalised linear mixed models (GLMMs). The complete list of candidate covariates and details of the analyses will be specified in a statistical analysis plan that will be reviewed and approved by the Principal Investigator prior to database lock. Analyses will be conducted using the most appropriate procedures in GenStat, R and STATA.

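### Outcome follow-up stops for anyone the Principal Investigator withdraws after randomisation, even without revoked consent, creating avoidable and possibly informative missing data that undermine the intention-to-treat aim

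*Protocol article*

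**What the plan says.** The rule is in the protocol article under Trial monitoring, Participant withdrawal/discontinuation. It applies where "it has been identified that a participant meets exclusion criteria during the study (e.g. active suicidality)", and/or where remaining in the study is judged not to be in the participant's best interests. In those cases "the Principal Investigator (a psychiatrist) will decide whether to withdraw the participant from the trial". After such a withdrawal, "No further data collection will occur, with the exception of the details regarding adverse events". The same section treats revocation of consent by the participant separately; only there is removal of data already collected an option.

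Under Statistical analysis plan, the primary analysis is "based on the intention-to-treat principle", which the article explains as analysing data as randomised and as stratified. The mixed model is described as "As well as accommodating missing values under the missing at random assumption". One analysis addresses departures from that assumption: "A sensitivity analysis, to assess the impact of missing 3-month data on the primary outcome", using a tipping-point approach.

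Four other places bear on the point:
- Table 1 schedules SIDAS and SADQ-C at screening only. AUDIT is taken at screening and then at 3, 6 and 12 months.
- Recruitment and screening lists participants, Researcher 2 and the study statistician as blind. It does not list the Principal Investigator.
- Adverse events requires enquiry "during each R2C session/control check-in and at each point of follow-up contact". The questions in Table 2 include "Has your mood changed".
- Loss to follow-up says that a participant who cannot be reached is tried again at the next time point unless that person actively withdraws.

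**The concern.** Leaving the study's calls and leaving outcome measurement are different events, and this rule ties them together. The participant's willingness to be assessed plays no part. Data that could have been collected are lost because of something that happened after randomisation, at the discretion of someone not stated to be blind to arm.

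The reason for the loss may be related to outcome. Active suicidality is the example given, and it has no scheduled measurement after screening that the model could use to explain why the value is missing. Missing at random is therefore doubtful for these participants. At stake are the 3-month AUDIT comparison, the 6- and 12-month AUDIT, K10 and quality of life, and the QALY comparison over 12 months. The protocol makes more effort to recover someone who does not answer the telephone than someone who was withdrawn and might still be willing.

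**Working it through.** **The plan's own figures.** 120 evaluable per arm with about 30% drop-out gives 120 / 0.70 = 171.4, rounded up to 172, as stated. The intraclass correlation is 23.8 / (23.8 + 49.8) = 0.323, as stated. For the 3-month contrast, the SD of change is √(2 × 49.8) = 9.98. With 120 per arm and a difference of 8 − 4 = 4, power by normal approximation is 87.4% (87.1 to 87.3% by non-central t), against the stated 85%. The stated figure is slightly conservative and does not affect this point.

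**What a withdrawn participant contributes.** R2C contact falls in weeks 1 to 6 and control contact in weeks 1 to 4 (Table 1), and the first post-baseline AUDIT is at 3 months. A participant withdrawn before then has one AUDIT value, from screening. The mixed model then treats that person as following the arm's trajectory, with no later AUDIT to correct it. A Timeline Follow-back record at 4–6 weeks may exist, but it belongs to a different outcome.

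**Illustrative bias.** The document gives no number or rate of investigator withdrawals, so the inputs below are assumptions. Let w be the share of an arm withdrawn before 3 months, and D the number of AUDIT points by which their change is worse than that of those retained, taken as equal in both arms. An arm's mean change is misstated by w × D, so the bias in the between-arm comparison is

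bias towards R2C = (w in R2C − w in control) × D.

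| w in R2C | w in control | D | Bias (points) | Share of 4 |
|---|---|---|---|---|
| equal | equal | any | 0 | 0% |
| 2% | 1% | 8 | 0.08 | 2% |
| 3% | 1% | 8 | 0.16 | 4% |
| 5% | 2% | 12 | 0.36 | 9% |
| 5% | 0% | 12 | 0.60 | 15% |

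Exchanging the two shares reverses the sign, so the same range applies against R2C. For scale, the standard error of the contrast is 9.98 × √(2/120) = 1.29, so the extreme case of 0.60 is 0.60 / 1.29 = 0.47 standard errors.

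**Precision.** If such withdrawals came on top of the 30% allowance, the evaluable number per arm would fall from 172 × 0.70 = 120.4 to 172 × 0.68 = 117.0 (2% more) or 172 × 0.65 = 111.8 (5% more). Power would go from 87.5% to 86.5% or 85.0%. The loss is minor; possible bias is the main issue.

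**The case against.** Three stronger readings are tempting, and the document supports none of them.

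*That the rule contradicts intention-to-treat.* The article defines the principle as analysis as randomised. Nothing in the withdrawal section removes an investigator-withdrawn participant from that set or deletes earlier data, and the analysis section expects some withdrawals. What it produces is missing data.

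*That it removes the worst outcomes.* The stated ground is an exclusion criterion or best interests, not deterioration or a poor AUDIT. A history of psychosis that comes to light late would also qualify and is not a worsening. Starting other treatment is an exclusion at screening only. No AUDIT level is given for such participants.

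*That more R2C participants would be detected, so the bias favours R2C.* R2C has four to six counselling sessions and control has four check-ins under 5 minutes, so unequal detection is possible. But the same adverse event and mood questions are prescribed in both arms, researchers as well as counsellors are trained to respond to suicide risk, and a blinded assessor follows both arms on the same schedule. If R2C lowers distress, more controls could meet the criteria and the bias would run the other way. One passage leans towards unequal detection: under Treatment integrity, the control script is meant to confine the call to past-week pamphlet use. That does not fit the adverse event questions set for the same calls.

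It can also be said that numbers are likely to be small, because high SIDAS and SADQ-C scores are excluded at screening; that the tipping-point analysis addresses this mechanism for the primary outcome; and that ending the assessments may itself be part of a best-interests decision. All three are fair. They limit the size of the problem and shape the fix. They do not justify giving up data from a participant who is willing and for whom a call is not considered harmful. A tipping-point analysis shows how fragile a result is, but cannot recover a value that was never collected.

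**Conclusion.** The point holds as a modest but worthwhile improvement. The rule creates avoidable and possibly informative missing outcomes, which weakens the intention-to-treat aim without contradicting it. Neither the size nor the direction of bias can be derived from the document. On assumed shares of 0 to 5% per arm and a deficit of 4 to 12 AUDIT points, with equal deficits in both arms, the bias runs from 0 to about 0.6 points in either direction, or 0 to 15% of the planned difference. It is zero when the shares are equal. The stated sensitivity analysis covers the 3-month primary outcome only; the full statistical analysis plan, not shown here, may say more, but no analysis plan can supply values the protocol says not to collect.

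**What to change.** Amend Participant withdrawal/discontinuation to separate withdrawal from study intervention calls from withdrawal from outcome follow-up. Where the participant has not revoked consent, and the follow-up call itself is not judged to be against that person's interests, keep the 3-, 6- and 12-month outcome calls, or at least the 3-month AUDIT, and analyse the data as randomised. Report investigator withdrawals by arm, with reasons and timing. Reconcile the control-call script under Treatment integrity with the adverse event questions in Table 2 and under Adverse events. Who is withdrawn, and how they are referred, stays as it is.

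The cost is a short amendment, consent wording and a few extra calls. The sample size stays at 172 per arm. The benefit reaches only those still in follow-up or not yet enrolled: Trial status gives 285 of 344 randomised, leaving 59 to recruit, with the last 12-month assessment expected in November 2020. For anyone already withdrawn under the present rule, only reporting by arm and the tipping-point analysis remain.

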### Statistical methods

#### Sample size estimation

A pilot study of an earlier version of the telephone-delivered intervention examined outcomes to a 3 month follow-up [42]. Thirty-four individuals concerned about their drinking were referred to the program and completed an average of 5.5 sessions. Participation in the intervention demonstrated significant reduction in alcohol problem severity (AUDIT score) and improvement in psychological distress (Kessler Psychological Distress Scale [K10] score). Treatment satisfaction and counsellor rapport scores were comparable to those found in face-to-face treatment. Using data from the pilot work, we found that the between-subject variance component in the AUDIT score was 23.8, the within-subject variance component was 49.8 (intraclass correlation [ICC] = 0.323) and the estimated improvement (decline) in the AUDIT score was 11.2 (standard error [SE] = 1.69). The calculation of the sample size used these estimates of the variance components, from the single-arm pilot study, and was based on the power of the *F* test for the overall time by treatment arm interaction and the power of the *t* test for the interaction contrast of primary interest, namely, baseline versus 3 months by treatment arm; calculations used the “apower” procedure for the non-central *F* distribution, and the “cut” function for the non-central *t* distribution in the GenStat statistical package [59].

We estimate, conservatively, that by 3 months, there will be an improvement (reduction of at least 8 on the AUDIT score) in the R2C arm and that the control arm could exhibit a modest improvement of 4. If these improvements are sustained at 6 and 12 months, then with 120 evaluable subjects in each arm and assuming independence between subjects and equicorrelation within subjects, the *F* test, conducted at the 5% significance level, for this treatment-by-time interaction will have 90% power (and the two-sided, 5% level, *t* test for the interaction contrast at 3 months will have 85% power). If these conjectured improvements by 3 months are not durable and, for example, deteriorate by 50% at 6 months, and the scores return, on average, to their baseline levels at 12 months, then this treatment-by-time interaction scenario will be detected with 85% power, and the power of the two-sided, 5% level *t* test for the interaction contrast at 3 months (the analysis of the primary outcome) remains unchanged at 85%.

The target sample size has been inflated from 120 per arm to 172 per arm to allow for approximately 30% drop-out, which is based on the attrition rate reported in a Swedish helpline study [26] and the experiences of the Chief Investigators where attrition in trials of face-to-face psychosocial interventions with this population average around 20% at 12 months [13].

